#### The PREDICT Bronchiolitis KT Study

The ‘Knowledge Translation (KT) in Australasian Paediatric Acute Care Settings Study’ (PREDICT Bronchiolitis KT study) (ACTRN12616001567415) was a multi-centre, cluster randomised controlled trial conducted in 26 Australian and New Zealand hospital Emergency Departments (EDs) and paediatric inpatient areas during the 2017 Southern Hemisphere bronchiolitis season (1st May to 30th November 2017), involving 3240 infants [4]. Of the 26 hospitals, 13 were randomised to the intervention group and 13 to the control group with all hospitals completing the trial. The intervention group received targeted, theory-informed interventions developed to address factors identified as influencing bronchiolitis management in Australia and New Zealand [32]. Interventions consisted of: identification of stakeholder meetings; clinical leads; Train-the-trainer workshop; educational materials with scripted, targeted messaging; other educational material consisting of a clinician video demonstrating how to talk with families about bronchiolitis, promotional materials, evidence fact sheets; and finally monthly audit and feedback (Table 1) [4, 33]. Both intervention and control group hospitals received printed and electronic copies of the Australasian Bronchiolitis Guideline.

**Table 1 Tab1:** Implementation Strategy Components used in the PREDICT Bronchiolitis KT Study [4, 33]

Intervention Components	Intervention Hospitals	Control Hospitals Post Trial^a^
Clinical leads	Four clinical leads for the duration of the study, included a medical and a nursing lead from each emergency department and inpatient paediatric areas. Key tasks included attending a 1-day train-the-trainer workshop, spearheading educational intervention and other educational materials delivery to all staff, supervising monthly audit completion and delivery of feedback, and management of study requirements.	Encouraged to allocate a medical and nursing lead, but no further guidance provided.
Stakeholder Meetings	Study team presented the Australasian Bronchiolitis Guideline to clinical leads, discussed local and international bronchiolitis management variations, reviewed results of the local audit, and discussed any local anticipated barriers, with the aim to gain site buy-in.	Nil.

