Train-the- trainer workshop	1-day workshop for clinical leads: discussed Australasian Bronchiolitis Guideline and evidence supporting recommendations, qualitative study identifying the facilitators and barriers of bronchiolitis management, implementation, and the development of interventions. Clinical leads received demonstrations on how to deliver educational interventions to their staff, outlines of study data timelines and requirements, and enabled planning time for clinical leads.	One-day workshop providing bronchiolitis intervention materials, with up to four clinical leads (medical and nursing) invited to attend. Discussion on what the aims of education materials were. Individual hospital data from the cluster RCT was presented (2014-2017). Feedback in relation to similar hospitals.
Educational intervention delivery	Key findings from qualitative study were presented in a PowerPoint with scripted messages stating use of behaviour change techniques most likely to effect change. Clinical Leads oversaw education delivery to medical and nursing staff using PowerPoint presentation. Within first month, aimed to educate 80% of staff and to ensure all staff educated ongoing education provided throughout duration of study.	PowerPoint presentation which was the same as presentation provided to the intervention hospitals.
Use of other educational materials	Clinical leads locally delivered promotional materials, evidence factsheets, clinician training video, and parent/caregiver information.	Education materials that were provided to the intervention hospitals.
Audit and feedback	Monthly audits of the first 20 bronchiolitis presentations, with report providing comparison between individual hospital results and top-performing site. Clinical leads disseminated report to their staff in written and verbal format; action planning with target setting encouraged.	Audit form and own hospital results from trial (4 years of data).
Ongoing facilitation	Weekly contact between clinical leads and study leads. Opportunities to ask questions via email.	Nil.

^a^delivered at trial completion in November 2018

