Findings of the PREDICT Bronchiolitis KT Study demonstrated that, when compared with control hospitals, intervention hospitals significantly improved adherence in management of bronchiolitis during the acute care period (first 24 hours of hospital presentation) for the five key low-value practices as per Australasian Bronchiolitis Guideline recommendations (14.1% adjusted risk difference, 95% CI, 6.5-21.7%; *P* < .001) [4, 34]. Specifically, during the acute care period (first 24 hours of hospital presentation), adherence to the Australasian Bronchiolitis Guideline recommendations with no use of salbutamol, glucocorticoids, antibiotics, adrenaline and CXRs, was 85% (95% CI, 82.6-89.7%) in the intervention group hospitals compared with 73% (95% CI, 65.3-78.8%) in the control group hospitals [4, 34]. At trial completion (November 2018), up to four nurses and doctors from each of the 13 control hospitals attended a 1 day workshop where they were given training and provided with intervention materials (Table 1). However, no on-going facilitation was provided.

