#### Quantitative study

##### Selection of patients with bronchiolitis

A retrospective patient medical record audit will be conducted by designated site study staff at each consenting site, under the supervision of site Principal Investigators. A list of all infants who presented between 1 January 2018 and 31 December 2019 with International Classification of Diseases 9th and 10th revision (ICD-9 or ICD-10) discharge codes for bronchiolitis (Table 2) will be retrospectively identified. To be eligible for inclusion, patients must be: aged less than 1 year (at time of presentation); AND have both an ED and discharge diagnosis of bronchiolitis. There are no patient-level exclusion criteria.

**Table 2 Tab2:** International Classification of Diseases (ICD) codes used for identifying patients

ICD code		Description
ICD–10	J21	Acute bronchiolitis
	J21-0	Acute bronchiolitis due to respiratory syncytial virus
	J21-1	Acute bronchiolitis due to human metapneumovirus
	J21-8	Acute bronchiolitis due to other specified organisms
	J21-9	Acute bronchiolitis, unspecified
ICD-9	466-11	Acute bronchiolitis due to respiratory syncytial virus
	466-19	Acute bronchiolitis due to other infectious organisms

Data for a total of 1800 infants (approximately 150 infants per site) will be collected at 2 years post-trial (2019), to address the primary outcome. Similarly, data from 1800 infants will be collected at one-year post-trial (2018). If a site has less than 150 infant presentations per year, 100% of eligible infants will be selected. If a site has more than 150 infant presentations per year, a random sample of 150 infants per year will be selected by an independent statistician using computer software.

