#### Outcome measures for quantitative study

Primary Outcome:Adherence with all five Australasian Bronchiolitis Guideline Recommendations (composite outcome) known to have no benefit (salbutamol, glucocorticoids, antibiotics, adrenaline and CXR) when an infant presents with bronchiolitis in the acute care period (first 24 hours of hospitalisation) at two- years (2019) following the completion of the PREDICT Bronchiolitis KT Study in intervention hospitals [34];

Secondary Outcomes:2.Adherence with all five Australasian Bronchiolitis Guideline Recommendations (composite outcome) known to have no benefit (salbutamol, glucocorticoids, antibiotics, adrenaline and CXR) when an infant presents with bronchiolitis in the acute care period (first 24 hours of hospitalisation) at one- year (2018) following the completion of the PREDICT Bronchiolitis KT Study in intervention hospitals [34];3.Adherence with all five Australasian Bronchiolitis Guideline Recommendations (composite outcome) known to have no benefit (salbutamol, glucocorticoids, antibiotics, adrenaline and CXR) when an infant presents with bronchiolitis in the acute care period (first 24 hours of hospitalisation) at 3a) one- year (2019) following provision of study materials, study results, and ‘Train the Trainer’ education (composite of all five practices) [4, 34]; and 3b) one- year (2018) following the completion of the PREDICT Bronchiolitis KT Study in control hospitals [4, 34].

The periods of one- and two- years following delivery of the intervention will be measured from the post-trial completion date of 30th November 2017.

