### Data analysis

Analysis of the data from the medical record audit will occur at the patient level, according to the group (intervention/control) that hospitals were randomly allocated in the previous study [4]. Absolute and relative frequencies of no use of all five low-value practices will be calculated. Means and standard deviations or medians and interquartile range will be used to present continuous outcomes. The proportions of no use of all five low-value practices and its 95% confidence intervals will be calculated and presented by study group. *Exploratory Objectives* will be run to estimate the marginal differences in proportions of no use of all five low-value practices between the study groups, using Generalised Linear Mixed (GLM) [34]. If the GLM models do not converge, logistic regression with a clustered-robust standard error (hospital level) will be used to calculate odds ratios. *Exploratory Objectives* will examine adherence to the five individual practices (i.e, no use of all five low-value practices); difference between intervention and control groups in 2019; difference between intervention and control groups in 2018; and trends over time (Table 3).

**Table 3 Tab3:** Exploratory objectives

To determine:	
• The proportion of infants presenting to hospital with bronchiolitis in the acute care period^a^, at intervention group hospitals, who received care that adhered with each of the five individual Australasian Bronchiolitis Guideline Recommendations known to have no benefit^b^: a) two- years (2019) following delivery of a targeted intervention [34]; and b) one- year (2018) following delivery of an intervention designed to promote evidence-based practice adherence [34];	
• The proportion of infants presenting to hospital with bronchiolitis in the acute care period^a^, at control group hospitals, who received care that adhered with each of the five individual Australasian Bronchiolitis Guideline Recommendations known to have no benefit^b^: a) two- years (2019) following delivery of an intervention designed to promote evidence-based practice adherence [4, 34]; and b) one- year (2018) following delivery of bronchiolitis intervention [4, 34];	

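### The delivery clock and the Table 3 labels for control hospitals contradict the November 2018 control delivery date: most of control 2018 precedes delivery, and 2019 is the first year after it, not the second

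*Protocol article*

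**What the plan says.** Under Outcome measures for quantitative study, one sentence governs timing for all hospitals: "The periods of one- and two- years following delivery of the intervention will be measured from the post-trial completion date of 30th November 2017". It makes no exception for the control group.

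The control hospitals' delivery date appears twice in the section on the parent trial. Footnote a to Table 1 says that the control package was "delivered at trial completion in November 2018". The results paragraph says "At trial completion (November 2018), up to four nurses and doctors from each of the 13 control hospitals attended a 1 day workshop". The same section places the trial itself "during the 2017 Southern Hemisphere bronchiolitis season (1st May to 30th November 2017", so completion of the trial carries two dates a year apart.

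The labels given to control-hospital data differ from place to place:
- Secondary outcome 3a counts 2019 as the first year: "3a) one- year (2019) following provision of study materials, study results, and ‘Train the Trainer’ education".
- Secondary outcome 3b ties control 2018 to the end of the trial and does not mention delivery.
- Table 3 (under Data analysis), second objective, counts control 2019 as two years after delivery and control 2018 as "one- year (2018) following delivery of bronchiolitis intervention".
- The third item under Outcome measures for qualitative study lists 2018 to 2021 as the four years after delivery, for intervention and control hospitals alike.

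Records are drawn by calendar year from "A list of all infants who presented between 1 January 2018 and 31 December 2019".

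**The concern.** A single origin of 30 November 2017 cannot describe time since delivery in hospitals that received the package about a year later. Read literally, control care given before the workshop and materials existed at those hospitals would be reported as adherence one year after delivery. The first year with the package would be reported as the second. The same hospitals in the same calendar year, 2019, are one year after provision in outcome 3a and two years after delivery in Table 3.

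Aims ii and iv ask whether control hospitals improved and what contributed, so when they received the package decides how the control results are read. Under the Table 3 labels, a rise from 2018 to 2019 that followed the November 2018 workshop would appear as a change between the first and second year after delivery.

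**Working it through.** **Inputs, all from the protocol article**
- Clock origin: 30 November 2017 (Outcome measures for quantitative study).
- Control delivery: November 2018, day not given (Table 1 footnote a; parent-trial results paragraph). Both ends of the month, 1 and 30 November, are used.
- Audit window: 1 January 2018 to 31 December 2019 (Selection of patients with bronchiolitis).
- Season: 1 May to 30 November, stated for 2017. Using the same months for 2018 is an assumption.

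Months are days divided by 30.44.

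**Step 1. The plan's own labels.** Counted from 30 November 2017, calendar 2018 covers months 1.1 to 13.0 and calendar 2019 covers months 13.0 to 25.0. One year (2018) and two years (2019) are therefore right as time since the trial ended.

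**Step 2. Distance from the clock to control delivery.** From 30 November 2017 to 1 November 2018 is 336 days, and to 30 November 2018 is 365 days. For control delivery the clock starts 11 to 12 months early.

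**Step 3. Share of calendar 2018 before control delivery** = days from 1 January 2018 to delivery, divided by 365.
- Delivery on 1 November: 304/365 = 83%.
- Delivery on 30 November: 333/365 = 91%.

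**Step 4. Share of a May to November 2018 season before delivery** (214 days).
- Delivery on 1 November: 184/214 = 86%.
- Delivery on 30 November: 213/214 = 99.5%.

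**Step 5. Position of calendar 2019 after control delivery.**
- Delivery on 1 November: months 2.0 to 14.0.
- Delivery on 30 November: months 1.1 to 13.0.

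In both cases 2019 is essentially the first year after delivery. This agrees with outcome 3a and disagrees with Table 3.

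**Step 6. Does the sample size depend on this?** No. The stated half-width of 7% uses a proportion of 85%, an intra-cluster correlation of 0.11, a coefficient of variation of 0.16 and 12 hospitals of 150 infants. The design effect is 1 + ((1 + 0.16²) × 150 − 1) × 0.11 = 17.81. The half-width is 1.96 × √(0.85 × 0.15 × 17.81/1800) = 6.96%, which reproduces the stated figure. No date enters it.

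**The case against.** The strongest reply is that this is a labelling slip of narrow reach. Most of that reply stands.

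- Outcomes 3a and 3b already use the right anchors: provision for control 2019 and end of trial for control 2018. A reader might infer that the control secondary outcomes report pre-delivery care as post-delivery care. Their own wording does not do so.
- The between-group objectives in Table 3 are tied to the end of the parent trial, and Data analysis compares hospitals by their original allocation. They carry no delivery label to correct.
- A reader might also infer that a smaller 2019 difference would lead to a finding that the effect was not sustained. The a priori rule does not permit that. It compares each hospital with its own post-implementation result, allowing a fall of at most seven percentage points, and the between-group difference is exploratory.
- It is tempting to call control 2018 unexposed and the 2019 contrast early versus delayed delivery. Neither description fits. Both groups received the guideline during the trial. The later control package was also reduced: Table 1 lists no stakeholder meetings and no ongoing facilitation, and an audit form with the hospital's own trial results in place of monthly audit and feedback.
- Sampling is by calendar year, so no record is selected differently.

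What the reply does not remove is the contradiction itself. The clock sentence and the Table 3 control objective are current statements about outcomes and objectives, and the article's own delivery date makes them wrong. Correct wording in 3a and 3b shows that the right timing was known and was not carried through.

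**Conclusion.** The point holds for the clock sentence, the control objective in Table 3 and the third qualitative outcome, together with the two dates for trial completion. Followed as written, control care from a year that is 83% to 91% before delivery would be labelled one year after delivery, and control 2019 would be placed a full year too late. The wrong conclusion concerns the exploratory and qualitative results for control hospitals. The primary outcome is unaffected, given completion on 30 November 2017, and so are outcomes 3a and 3b, the sample size and the per-hospital sustainability rule.

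Assumptions:
- November 2018 is taken as the true control delivery date. It is stated twice, and outcome 3a agrees with it. If it were itself a slip for 2017, outcome 3a would be the wrong statement, so the passages must be reconciled either way.
- The percentages are shares of time. The share of sampled control infants seen before delivery depends on seasonality, which the article does not give. The season figures of 86% to 99.5% show the range under the May to November assumption.

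**What to change.** 1. Give trial completion one date throughout, and state the control workshop date separately in the parent-trial text and Table 1 footnote a.
2. Replace the single clock sentence with an origin for each group: trial end, 30 November 2017, for intervention hospitals, and the November 2018 workshop for time since delivery in control hospitals.
3. In Table 3 and in the third qualitative outcome, relabel control 2018 as essentially before delivery and control 2019 as the first year after delivery.
4. Beside the exploratory 2019 between-group difference, state that control hospitals had by then received a reduced package (workshop and materials, without ongoing facilitation). A difference smaller than in 2018 is then not by itself evidence of lost effect.

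Optional: a control contrast of 2019 against 2018, and a date filter on control records after the workshop in late 2018.

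The required changes are wording only. They need no new data, no further hospitals and no change to the sample size.

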### Data collection procedure

#### Medical record audit

Routinely collected bronchiolitis management data will be retrospectively extracted from medical records by designated site study staff. De-identified data extracted from the medical records will be entered into a standardised form in a Research Electronic Data Capture (REDCap) database by designated study staff at each hospital.

#### Sample size

The sample size for this medical record audit will depend on the number of participating hospitals and will be recalculated upon completion of the hospital recruitment stage. Based on our previous study [4], assuming an Intra-cluster Correlation Coefficient of 0.11, an expected proportion of no use of all five low-value practices) of 85% (based on results of the PREDICT Bronchiolitis KT Study) [4] and a Coefficient of Variation of cluster sizes of 0.16 [4], a total sample size of 1800 (obtained from 12 intervention hospitals (clusters) with an average size of 150 infants) will achieve a confidence interval (CI) half-width of 7% (95%CI: 78 to 92%). An equivalent number of infants, i.e. 1800 in total, will also be obtained from ~ 12 control hospitals (clusters) with an average size of 150 infants.

### Data analysis

Analysis of the data from the medical record audit will occur at the patient level, according to the group (intervention/control) that hospitals were randomly allocated in the previous study [4]. Absolute and relative frequencies of no use of all five low-value practices will be calculated. Means and standard deviations or medians and interquartile range will be used to present continuous outcomes. The proportions of no use of all five low-value practices and its 95% confidence intervals will be calculated and presented by study group. *Exploratory Objectives* will be run to estimate the marginal differences in proportions of no use of all five low-value practices between the study groups, using Generalised Linear Mixed (GLM) [34]. If the GLM models do not converge, logistic regression with a clustered-robust standard error (hospital level) will be used to calculate odds ratios. *Exploratory Objectives* will examine adherence to the five individual practices (i.e, no use of all five low-value practices); difference between intervention and control groups in 2019; difference between intervention and control groups in 2018; and trends over time (Table 3).

**Table 3 Tab3:** Exploratory objectives

To determine:	
• The proportion of infants presenting to hospital with bronchiolitis in the acute care period^a^, at intervention group hospitals, who received care that adhered with each of the five individual Australasian Bronchiolitis Guideline Recommendations known to have no benefit^b^: a) two- years (2019) following delivery of a targeted intervention [34]; and b) one- year (2018) following delivery of an intervention designed to promote evidence-based practice adherence [34];	
• The proportion of infants presenting to hospital with bronchiolitis in the acute care period^a^, at control group hospitals, who received care that adhered with each of the five individual Australasian Bronchiolitis Guideline Recommendations known to have no benefit^b^: a) two- years (2019) following delivery of an intervention designed to promote evidence-based practice adherence [4, 34]; and b) one- year (2018) following delivery of bronchiolitis intervention [4, 34];	
• The difference between control and intervention group hospitals in the proportion of infants presenting to hospitals with bronchiolitis who received care that adhered with each of the five individual Australasian Bronchiolitis Guideline Recommendations known to have no benefit^b^ in the acute care period: a) two- years (2019); following the completion of the PREDICT Bronchiolitis KT Study [4, 34]; and b) one- year (2018); following the completion of the PREDICT Bronchiolitis KT Study [4, 34];	
• The difference between control and intervention group hospitals in the proportion of infants presenting to hospital with bronchiolitis who received care that adhered with all five Australasian Bronchiolitis Guideline Recommendations known to have no benefit^b^ in the acute care period: a) two- years (2019) following the completion of the PREDICT Bronchiolitis KT Study (composite outcomes of all five practices) [4, 34]; and b) one- year (2018) following the completion of the PREDICT Bronchiolitis KT Study (composite of all five practices) [4, 34];	
• The trends in the proportions of infants presenting to hospital with bronchiolitis who received care that adhered with each of the individual five Australasian Bronchiolitis Guideline Recommendations known to have no benefit^b^ yearly from 2014 to 2019 in the acute care period, at control and intervention group hospitals [34].	

^a^ First 24 hours of hospitalisation, ^b^ no use of: i) salbutamol, ii) glucocorticoids, iii) antibiotics, iv) adrenaline, and v) chest x-ray

An a priori definition of sustained improvements will be based on the 7% median improvement achieved in the PREDICT Bronchiolitis KT Study [4]. Practices will be defined as sustained when there is either a maximum of a seven percentage point decrease or any level of improvement (i.e. -7% to infinity) from the participating hospital’s individual post-implementation results based on a composite outcome of the five low-value practices of interest [4, 34].

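### The primary 95% CI is not tied to the hospital clustering on which its precision was planned, and the stated 7% half-width rests on a normal quantile (about 7.8% with t for 12 hospitals)

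*Protocol article*

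**What the plan says.** The primary outcome is the proportion of infants in intervention hospitals in 2019 managed without any of the five low-value practices. It is a single-group quantity, and its precision is planned as a confidence-interval width.

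- **Sample size (quantitative study).** The calculation is made "assuming an Intra-cluster Correlation Coefficient of 0.11", with an expected proportion "of 85% (based on results of the PREDICT Bronchiolitis KT Study" and "a Coefficient of Variation of cluster sizes of 0.16". From these, "a total sample size of 1800 (obtained from 12 intervention hospitals (clusters) with an average size of 150 infants" is said to deliver the target: it "will achieve a confidence interval (CI) half-width of 7% (95%CI: 78 to 92" percent. The same section calls the figure provisional, since it "will be recalculated upon completion of the hospital recruitment stage".
- **Data analysis (quantitative study).** The section opens with "Analysis of the data from the medical record audit will occur at the patient level", by originally randomised group. For the proportions it says that "The proportions of no use of all five low-value practices and its 95% confidence intervals will be calculated and presented by study group". It names no method for that interval.
- **Where hospital-level methods appear.** The same paragraph then gives a generalised linear mixed model for the marginal differences between groups, labelled exploratory. If that does not converge, the fallback is logistic regression with hospital-level cluster-robust standard errors, reporting odds ratios.

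**The concern.** The two sections do not meet at the primary estimate. On the protocol's own inputs, variation between hospitals dominates the uncertainty: 1800 infants carry the information of about 101 independent ones. Yet the analysis text gives the exploratory contrasts a cluster-aware model and a fallback, and says only that the primary proportion and its interval will be calculated.

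The exploratory method does not carry over by itself. It is described for a difference between groups, and its fallback yields odds ratios, not a proportion for one group. An analyst working from this text could produce a simple binomial interval for the main result without departing from any sentence in it.

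The second matter is the planned figure. With 12 hospitals, the between-hospital variance is estimated on 11 degrees of freedom. A half-width obtained with 1.96 is therefore somewhat smaller than the study can expect to report from a method suited to so few clusters.

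**Working it through.** **Inputs**, all from the Sample size section: p = 0.85; ICC = 0.11; coefficient of variation of cluster size CV = 0.16; k = 12 hospitals; mean size m = 150; N = 12 × 150 = 1800; 95% two-sided interval. The section states neither a design-effect formula nor a quantile. The standard formula for unequal clusters is used below.

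**1. Reproduce the stated 7%.**

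- Design effect = 1 + ((CV² + 1)m − 1) × ICC = 1 + ((0.0256 + 1) × 150 − 1) × 0.11 = 1 + 152.84 × 0.11 = 17.81.
- Effective sample size = 1800 / 17.81 ≈ 101.
- SE = √(0.85 × 0.15 / 1800 × 17.81) = 0.0355.
- Half-width with z = 1.96: 1.96 × 0.03552 = 6.96%, which rounds to the stated 7% (78 to 92%).

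Leaving out the CV term gives a design effect of 17.39 and a half-width of 6.88%, which also rounds to 7%. So the planned interval includes clustering and uses a normal quantile.

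**2. The same calculation with t.**

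| Intervention hospitals (150 each) | z half-width | t half-width (k − 1 df) |
|---|---|---|
| 12 | 6.96% | 7.82% |
| 13 | 6.69% | 7.44% |
| 14 | 6.45% | 7.10% |
| 15 | 6.23% | 6.81% |

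For 12 hospitals, 2.201 × 0.03552 = 7.82%, or about 77.2 to 92.8%. At 150 infants per hospital, a t-based half-width of 7.0% or less would need 15 hospitals. The earlier trial randomised 13 to intervention.

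**3. What a simple proportion would give.**

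- SE = √(0.1275 / 1800) = 0.00842, so the half-width is 1.96 × 0.00842 = 1.65% (83.4 to 86.6%).
- Ratio of the clustered to the unclustered width = √17.81 = 4.22.
- Approximate coverage of the unclustered interval = 2Φ(1.96 / 4.22) − 1 = 36%.

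**4. Simulation check.** This used 200,000 runs of 12 hospitals, beta-binomial outcomes with p = 0.85 and ICC = 0.11, and roughly normal cluster sizes with mean 150 and SD 24 (= 0.16 × 150).

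| Interval | Coverage |
|---|---|
| Unclustered binomial | 35.3% |
| Hospital-level robust variance, z | 90.1% |
| Hospital-level robust variance, t on 11 df | 92.6% |

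**The case against.** A reader might infer something stronger: that the primary interval is planned without clustering and is, as written, four times too narrow. The article does not support that.

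- It names no method for the interval, clustered or not.
- Patient-level analysis describes the unit of analysis, not the variance estimator. The mixed model and the cluster-robust regression in the same paragraph are themselves patient-level analyses.
- The only interval actually written, 78 to 92%, already contains a design effect of about 17.8. The factor of 4.2 and the 36% coverage belong to a simple binomial calculation that the sample size section points away from.

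It can also be said that a condensed article commonly leaves the variance method to a statistical analysis plan, which is not shown here. Mere silence would indeed be no finding. What remains is narrower: the article does set out methods, down to a non-convergence fallback, and places hospital-level methods only on exploratory contrasts while the main estimate is planned on a large design effect.

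On the quantile, the objection has some force. The normal quantile is inferred from reproduction. The difference is under one point. The ICC is itself uncertain: an ICC of 0.087 would give 7.0% even with t (design effect 1 + 152.84 × 0.087 = 14.30; SE 0.0318; 2.201 × 0.0318 = 7.0%). The t interval does not reach 95% in the simulation either. The planned recalculation will also change the figure, but a new hospital count does not by itself correct the quantile.

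Finally, sustained practice is defined by each hospital's change from its own post-implementation result, allowing at most a seven-point fall. That rule does not use the pooled interval, so no sustained or not-sustained classification turns on this point.

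**Conclusion.** The point holds in two limited parts.

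1. The analysis text does not tie the primary interval to the clustering on which its precision was planned. The consequence is conditional: a simple proportion would report about ±1.65 points where the plan's own assumptions imply about ±7, with coverage near 36%. The same gap affects the secondary group proportions.
2. The stated 7% is modestly optimistic. With t on 11 degrees of freedom it is about 7.8% for 12 hospitals, 0.9 points wider than the 6.96% behind the stated figure. With all 13 it is about 7.4%. This part is minor on its own.

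Both rest on the protocol's ICC, CV and expected proportion, on the standard design-effect formula, and on the inference that 1.96 was used. The effect falls on the reported primary estimate and the certainty attached to it, not on the hospital-level definition of sustained practice.

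**What to change.** Add one sentence to the Data analysis section: the primary and secondary group proportions and their 95% intervals will be obtained by a hospital-clustered method, with t limits on the number of hospitals minus one degrees of freedom. The method could be cluster-robust variance at hospital level, or a mixed logistic model with marginal standardisation; name one. If the statistical analysis plan already says this, align the two texts.

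In the Sample size section, state the quantile used and restate the planned half-width as about 7.8% (roughly 77 to 93%) for 12 hospitals, to be updated on the same basis at the planned recalculation.

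The cost is one sentence of analysis text and a slightly less favourable stated precision. No extra data are needed.
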